### Exposures

Data on all primary care prescriptions from 90 days prior to pregnancy through to the end of pregnancy, including those that have been initiated in secondary care and continued in primary care, will be extracted. Prescribing patterns will be assessed throughout pregnancy and by trimester and 90 days prior to pregnancy start. Trimesters will be defined as per the CPRD pregnancy register. Medications will be classified using British National Formulary (BNF) and Anatomical Therapeutic Chemical (ATC) systems.

### Outcomes

Adverse outcomes will be identified using coded data from primary care, hospital admissions, and linked datasets. Outcomes will be grouped into maternal, fetal, and infant categories, based on the Core Data Elements for pregnancy pharmacovigilance developed by the European Network of Teratology Information Services and ConcePTION consortium [6,14,19] (Table 1).

**Table 1 pone.0349045.t001:** Outcome groups to be extracted from health records.

**Maternal**	Maternal medical conditions arising in pregnancy
	Maternal delivery complications
	Maternal post-partum complications
	Maternal death
**Fetal**	Molar pregnancy
	Ectopic pregnancy
	Miscarriage
	Premature delivery
	Congenital anomaly
	Stillbirth
**Infant**	Small-for-gestational-age at delivery
	Large-for-gestational-age at delivery
	Neonatal death
	Infant death
	Hospital admissions

The maternal medical conditions arising in pregnancy outcomes will include: gestational diabetes; hypertensive disorders of pregnancy; venous thrombotic episode; depression/anxiety/psychosis; pulmonary oedema; acute kidney injury; stroke; maternal infections; antepartum haemorrhage. The congenital anomaly outcome will include major congenital anomaly subgroups of heart, limb, kidney and urinary tract, digestive system, nervous system, abdominal wall, respiratory, and oro-facial clefts.

For our clinical outcomes, some of the relevant code lists have already been developed and will be accessed from code repositories and publications and reviewed by our clinical team, e.g., pre-eclampsia [20], stroke [21], congenital anomalies [22]. Some pregnancy related outcomes are also included in the pregnancy register data received from CPRD, e.g., stillbirth, miscarriage, ectopic pregnancy, molar pregnancy [15]. For outcomes with no appropriate published codelists, we will develop new code lists.

### Covariates

Ethnicity will be based on self-reported ethnicity recorded in HES, or where HES ethnicity is missing, the most recent recorded ethnicity in primary care records. Socio-economic status will be measured by the linked Index of Multiple Deprivation data. Geographic regions will be defined as the Office of National Statistics (ONS) regions assigned to each practice by CPRD. Comorbidities (e.g., asthma, diabetes, migraine, depression/anxiety) at the start of pregnancy will be extracted from CPRD and HES codes.

## Statistical analysis

### Objective 1: Descriptive analysis

Individual medications will be grouped into summary categories broadly based on BNF chapter and section (S1 Table) [23]. Binary variables will be created for whether a medication from each of the categories was prescribed at any time during the pregnancy, each trimester of pregnancy individually, and for the three-month period prior to the start of pregnancy. Rates of prescribing of each medication category will be calculated per 1000 pregnancies.

To look at trends over time, rates of prescribing will be calculated for each year separately, with a pregnancy assigned to a single year based on the start date of the pregnancy.

Factors influencing the prevalence of prescribing of medication groups during pregnancy will be investigated by modelling whether a prescription was issued for a given medication group during pregnancy, using multivariable logistic regression models including variables such as maternal age, ethnicity, geographical region, deprivation, and comorbidities.

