## Materials and methods

The overarching aim of this study is to identify medications that may be harmful to the mother, fetus, or infant, when prescribed during pregnancy.

The specific objectives are:

To describe temporal trends in medications prescribed during pregnancy in primary care in England over the past 20 years, and to examine variation by maternal age, ethnicity, socio-economic status, geographical region, and comorbidities.To apply Bayesian signal detection methods to identify medications potentially associated with adverse maternal, fetal, or infant outcomes.To integrate signal detection results with existing scientific evidence and expert and patient input in order to prioritise medications requiring further investigation.To conduct detailed retrospective cohort studies of three prioritised medications to quantify associations with adverse outcomes after adjusting for confounding.

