**Fig 1 pone.0349045.g001:**
[figure not shown]
Study population and data sources for exposures and outcomes.

We will use data from the CPRD pregnancy register to identify pregnancy episodes and estimated delivery dates and the Mother-Baby link to identify infant outcomes [15,16]. CPRD contains data contributed by GP practices using Vision (Gold) and EMIS (Aurum) clinical systems. The CPRD pregnancy register has been validated against linked HES and the ONS live birth data [15]. Data will be linked to HES data, ONS death registration data, and IMD data.

The study protocol was approved by CPRD’s Research Data Governance group (Ref: 24_004518). Based on these approvals individual patient consent was not required.

Analyses will be conducted within CPRD Safe (trusted research environment).

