### Study population

The study will include women in the CPRD pregnancy register who have been registered for at least six months before the start of each pregnancy to ensure sufficient recording of long-term health conditions. An individual woman can contribute more than one pregnancy. The CPRD pregnancy register uses an algorithm based on primary care records to generate information on likely pregnancies, dates, and outcomes. This pregnancy register has been validated and can be supplemented with hospital admissions data to further improve accuracy of information on pregnancy dates and outcomes [15,17,18].

Non-singleton pregnancies will be excluded. Mother and baby will be followed up for up to one year after birth to look at maternal post-partum and infant outcomes.

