**Prevalence of use overall and in under-represented groups**

Commonly prescribed medications will be given priority over those prescribed more infrequently. We will also be able to identify any medications prescribed more frequently in under-represented socio-demographic groups from our results in objective 1, which will be an additional priority criterion.

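### Objective 1 names a pregnancy-level logistic model for region, which is a practice-level factor, with no allowance for correlation within practice; fitted as written, the regional confidence intervals will be too narrow

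*Protocol article*

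**What the plan says.** The objectives listed under Materials and methods make regional variation an explicit aim; Objective 1 is in part "to examine variation by maternal age, ethnicity, socio-economic status, geographical region, and comorbidities".

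Under Statistical analysis, Objective 1, the analysis consists of "modelling whether a prescription was issued for a given medication group during pregnancy". The method and its covariates are given as follows: "using multivariable logistic regression models including variables such as maternal age, ethnicity, geographical region, deprivation, and comorbidities". The unit is the pregnancy, the outcome is binary and region is a named covariate.

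Two other statements fix the data structure. Covariates: "Geographic regions will be defined as the Office of National Statistics (ONS) regions assigned to each practice by CPRD". Data source: "CPRD contains data contributed by GP practices using Vision (Gold) and EMIS (Aurum) clinical systems". Study population adds a second level of clustering: "An individual woman can contribute more than one pregnancy".

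The article does not say how correlation within practice, or within woman, is to be handled in these models.

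**The concern.** The outcome is a prescribing act in general practice. Practices differ in prescribing habits and in recording, so pregnancies in one practice resemble each other more than pregnancies in different practices. For a factor that varies within practice, part of that shared variation cancels in the comparison. For region none of it does, because region is constant within practice. The amount of independent information on a regional contrast is therefore governed mainly by the number of practices, whereas a standard logistic regression takes it from the number of pregnancies.

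Point estimates are not the main issue; interval width is. Objective 1 covers about 20 years, so a practice may contribute many pregnancies, and the understatement of the standard error grows with that number even when the ICC is small. At stake is whether the reported regional differences, one of five sources of variation the study sets out to examine, can be told apart from the chance mix of practices in each region.

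**Working it through.** The article states no sample size, significance level, ICC, number of practices or pregnancies per practice for Objective 1, so there is no planned figure to reproduce. What follows illustrates the size under stated assumptions.

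**From the article:** region is constant within practice (Covariates); the model is logistic, with one record per pregnancy and region as a covariate (Objective 1).

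**Assumed:** m, the pregnancies per practice (50 to 1,000); ρ, the practice ICC for a prescription (0.001 to 0.05); nine regions for the joint test; no true regional difference.

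**Formulas**
- Design effect for a covariate constant within practice: DE = 1 + (m − 1)ρ.
- True size of a nominal 5% contrast of two regions: 2 × [1 − Φ(1.96/√DE)].
- True size of a nominal 5% joint test over nine regions: P(χ² on 8 df > 15.51/DE).

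**Three worked cases, two-region contrast**
- m = 50, ρ = 0.001: DE = 1 + 49 × 0.001 = 1.049; 1.96/√1.049 = 1.91; true size 0.056.
- m = 200, ρ = 0.01: DE = 1 + 199 × 0.01 = 2.99; 1.96/√2.99 = 1.13; true size 0.257. The correct standard error is √2.99 = 1.73 times the one the model reports.
- m = 1,000, ρ = 0.05: DE = 1 + 999 × 0.05 = 50.95; 1.96/√50.95 = 0.27; true size 0.784.

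**Range (two-region contrast / joint 8-df test)**

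| m | ρ = 0.001 | ρ = 0.01 | ρ = 0.05 |
|---|---|---|---|
| 50 | 0.056 / 0.064 | 0.108 / 0.238 | 0.291 / 0.810 |
| 200 | 0.073 / 0.114 | 0.257 / 0.737 | 0.554 / 0.994 |
| 500 | 0.109 / 0.242 | 0.423 / 0.957 | 0.700 / 1.000 |
| 1,000 | 0.166 / 0.458 | 0.554 / 0.994 | 0.784 / 1.000 |

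At ρ = 0 both tests have their nominal 0.05.

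**Check by simulation.** Beta-binomial data were generated with nine regions, 40 practices per region, prescribing prevalence 5% or 30%, m = 200 or 500, ρ from 0 to 0.05, no true regional difference and 2,000 runs per cell. At m = 200 and ρ = 0.01 the unclustered two-region contrast rejected in 0.247 (5% prevalence) and 0.258 (30%) of runs, and the unclustered joint test in 0.74 and 0.73, in line with the formulas. With practice accounted for, rejection over all cells was 0.046 to 0.068 for the cluster-robust contrast and 0.042 to 0.056 for a practice-level F test.

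The simulation has no other covariates. Adjustment for age, ethnicity, deprivation and comorbidity may remove part of the variation between practices, so ρ should be read as the ICC that remains after adjustment.

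**The case against.** The strongest objection is that the point is read from silence. The article does not call the regression ordinary, does not say that pregnancies are treated as independent and names no variance estimator. Its covariate list is open, and a GEE or a random-intercept logistic model would also fit the wording. It is a condensed article, and a fuller approved protocol or an analysis plan may specify clustering. That stands as a limit: the article does not show that clustering will be ignored. It does not remove the point. The article commits to outcome, unit, method and covariates, and the method as named does not suit a covariate that the article itself places at practice level.

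A reader might go further and infer that regional differences will be declared from practice-to-practice variation alone. The article does not support that. Objective 1 is descriptive, with no test, significance level or rule for declaring a difference, and real regional differences may exist. The error rates above measure how far the intervals mislead; they do not predict the study's conclusions.

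A reader might also carry the point over to deprivation, ethnicity and the prioritisation in Objective 3. Those two factors can vary within a practice, so the design effect used here does not apply to them; any effect is likely smaller and was not calculated. The Objective 3 criterion is to "identify any medications prescribed more frequently in under-represented socio-demographic groups from our results in objective 1". It does not name region and sets no statistical threshold, so no prioritisation decision is shown to change.

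Finally, ICC and cluster size are assumed. At the benign end (ρ = 0.001, m = 50) the problem is negligible.

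**Conclusion.** The point holds in a limited form. The Objective 1 model, fitted as named, gives confidence intervals for region that are too narrow, because region is set by practice and no allowance for correlation within practice is stated. The true error of a nominal 5% two-region contrast runs from about 6% to about 78% over the assumed range, with about 26% at an ICC of 0.01 and 200 pregnancies per practice. A joint test of region is affected more. All of these figures depend on an ICC and a cluster size that the article does not give. The conclusion concerns interval width for one descriptive factor. It does not reach the signal detection, nor the cohort studies, whose analysis plans are deferred.

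**What to change.** In Objective 1, keep the multivariable logistic model and add one sentence: standard errors will be cluster-robust, or obtained by GEE, with general practice as the cluster. This keeps marginal odds ratios. Because practice is the higher level, it also covers repeat pregnancies of a woman who stays in one practice, though not those of a woman who moves between practices.

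Do not enter practice as a fixed effect: region is constant within practice and would be absorbed. A practice random intercept would also allow for the correlation, but its odds ratios are conditional on practice and answer a slightly different question; if it is preferred, the plan should say so.

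The cost is one sentence in the plan and one option in the model call, provided the extract carries a practice identifier, which the article does not state and the study team should confirm. The downside is wider intervals, chiefly for region.

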### Objective 2: Signal detection

Adverse outcomes will be defined as above. Exposures will be prescriptions of individual active ingredients of medications. The estimated dates of pregnancy will be used to identify any medications prescribed in the three months prior to pregnancy or during pregnancy, and analyses will be run for each trimester separately as well as for the three-month period prior to pregnancy.

We will apply standard Bayesian signal detection models using the Information Component (IC) [24–26]. This method is based on comparing the frequency of occurrence of the outcome of interest in mothers prescribed the medication of interest compared to the frequency of occurrence of the outcome of interest in mothers not prescribed the medication of interest for each medication/outcome pair. IC values that are positive indicate that the outcome and prescribed medication occur more frequently together than would be expected due to chance if both events were independent. In brief the observed counts (a,b,c,d from a two-by-two table) are assumed to have a Multinomial distribution (pa,pb,pc,pd,n). With a Dirichlet prior distribution for pa pb pc and pd the corresponding posterior distribution is also a Dirichlet distribution. Assuming an uninformative prior likelihood, 100,000 random samples from the proposed posterior Dirichlet distribution can be generated and the median IC with its 95% credible intervals obtained [27]. Pairs with a positive lower 95% credible interval have sufficient evidence that they are occurring more frequently than would be expected due to chance and are classified as signals.

Our new method of hierarchical modelling will then use these results to identify groups in the data using bi-clustering techniques. For this method, pairs with a positive lower 90% credible interval using the IC are considered ‘potential signals’. A group is defined as containing all medication/outcome pairs where all medications in the group have a potential signal with the same outcomes in the group. Medications with similar pharmacological properties are likely to be in the same groups, but the actual group membership is determined purely by the data. These groups will then be used to calculate an observed to expected ratio, adjusted for groupings, for each medication/outcome pair.

$$\begin{array}{c} Log(Proportional\;Reporting\;Ratio\;\left(PRR)\right)=\;\frac{Observed\;Frequency\;of\;Outcome\;and\;Medication}{Expected\;Frequency\;of\;Outcome\;and\;Medication} \end{array}$$

As with the IC, values that are positive indicate that the outcome and exposure occur more frequently together than would be expected due to chance if both events were independent [24,25].

The log(observed/expected) for each medication/outcome is assumed to have a gaussian distribution where the mean has two components – one that is determined by the mean of all medications and outcomes in the same group and an additional component specific to each medication/outcome. This assumes that similar medications may have similar safety profiles and will result in all the medication/outcomes in a specific group having more similar results than if the Log(observed/expected) was calculated independently for each pair. As with the IC, the posterior distribution is derived from the combination of the prior and the likelihood from the observed data. However, as the posterior distribution is not the same as the prior distribution Monte Carlo Methods need to be employed to derive it. Any medication/outcome pairs with the 95% credible interval above 1 will be interpreted as generated signals.

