**Available evidence**

For all signals identified we will annotate them with information from the BNF, UKTIS, Reprotox, TOXBASE and DART. We will add information from searches on PubMed and Ovid.

Each individual medication-outcome pair will be annotated as

iknown harmful effectiiknown indication effect (association between the reason the medication is taken and the outcome)iiiunknown – limited evidence for specific pairivunknown – limited evidence for composite exposure (broad medication groupings) and/or composite outcome (grouping of specific outcomes)vunknown – no evidence

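### For maternal conditions that arise in pregnancy, the signal-detection exposure rule does not require the prescription to precede the outcome, so treatments can appear as strong false signals

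*Protocol article*

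**What the plan says.** Under Objective 2: Signal detection, exposure is a prescription of an active ingredient, placed by the estimated pregnancy dates: "The estimated dates of pregnancy will be used to identify any medications prescribed in the three months prior to pregnancy or during pregnancy". The sentence continues that "analyses will be run for each trimester separately as well as for the three-month period prior to pregnancy". The IC rests on "comparing the frequency of occurrence of the outcome of interest in mothers prescribed the medication of interest compared to the frequency of occurrence" in mothers not prescribed it, using the four counts of a two-by-two table.

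Under Outcomes, one of the 15 groups in Table 1 consists of conditions that develop while the exposure windows are open: "gestational diabetes; hypertensive disorders of pregnancy; venous thrombotic episode; depression/anxiety/psychosis; pulmonary oedema; acute kidney injury; stroke; maternal infections; antepartum haemorrhage".

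Two thresholds follow. For a signal: "Pairs with a positive lower 95% credible interval have sufficient evidence that they are occurring more frequently than would be expected due to chance". For entry to the grouping step: "pairs with a positive lower 90% credible interval using the IC are considered" potential signals. Group membership is then decided by the data alone, and the log observed-to-expected ratio of each pair is pulled towards its group mean. The Abstract says that confounders are not handled at this stage.

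Under Objective 3, each signal is later annotated. One label is a known indication effect, explained as "association between the reason the medication is taken and the outcome".

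**The concern.** Several of these maternal conditions are commonly treated with prescribed medicines once diagnosed. A woman diagnosed and then treated in the same trimester is counted as exposed with the outcome. Under the rule as stated, so is a woman diagnosed in one trimester and treated in the next. The association then runs from outcome to drug, which is not evidence of harm.

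At stake are the order of the signal list, the population attributable risks that feed prioritisation, and the group means to which other drugs are shrunk. For a medicine used both before and after onset, a label added afterwards cannot separate a real effect from treatment. The lists of biases under Objective 3 and under Limitations name indication, co-medication, over-the-counter use and miscoding, but not prescriptions that follow the outcome.

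**Working it through.** The article gives no outcome rate, drug-use rate or cohort size, so there is no stated figure to reproduce. All inputs below are assumptions, applied to the article's own IC.

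**Setup.** Outcome risk p; background use b of a drug with no effect; fraction f of the remaining cases prescribed it after diagnosis.

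- Exposed cases = N·p·(b + (1 − b)·f)
- Exposed non-cases = N·(1 − p)·b
- O/E = exposed cases / (all exposed × p), and IC = log2(O/E)

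**One case in full.** N = 500,000, p = 0.05, b = 0.005, f = 0.02.

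- Exposed cases = 25,000 × (0.005 + 0.995 × 0.02) = 622.5
- Exposed non-cases = 475,000 × 0.005 = 2,375
- O/E = 622.5 / (2,997.5 × 0.05) = 4.15; IC = 2.05

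**Range over f** (Dirichlet posterior, uniform prior):

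| Cases prescribed after diagnosis | Median IC | Lower 95% limit |
|---|---|---|
| 0% | 0.01 | −0.25 |
| 0.5% | 0.93 | 0.76 |
| 2% | 2.05 | 1.95 |
| 10% | 3.39 | 3.35 |
| 50% | 4.07 | 4.05 |

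For comparison, truly harmful drugs used in 1% of pregnancies give IC 0.58 (relative risk 1.5), 0.99 (2) and 1.56 (3). The ceiling at a 5% outcome is log2(1/0.05) = 4.32.

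**Other outcome rates.** With 10% of cases treated and b = 0.005, the IC is 4.12 for a 1% outcome and 2.81 for a 10% outcome, against 1.56 for relative risk 3 in both. In every scenario run (outcome 0.1% to 10%, background use 0.1% or 0.5%, 100,000 to 1,000,000 pregnancies), treating at least 10% of cases outranked relative risk 3.

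**Attributable risk.** Assume p = 0.05, 30% of cases exposed through treatment, and 0.2% use in non-cases.

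- Exposed share = 0.015 + 0.95 × 0.002 = 0.0169
- Risk in exposed = 0.015 / 0.0169 = 0.888
- Risk in unexposed = 0.035 / 0.9831 = 0.0356; ratio 24.9
- Attributable fraction = 0.30 × (1 − 1/24.9) = 0.29, when the true value is zero

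**Grouping.** Take three treatments with O/E 19.27, 18.81 and 16.83, and one weak pair with O/E 1.35. The geometric mean is 9.53. Shrink the weak pair on the log scale with weight B = s²/(s² + τ²), where s² = 1/observed count and τ is the within-group SD, which the article does not state.

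- 400 exposed: observed = 400 × 0.05 × 1.35 = 27, so s² = 0.037. For τ = 0.3, B = 0.037/(0.037 + 0.09) = 0.29 and O/E becomes 2.39. For τ = 0.6 and 1.0 it becomes 1.62 and 1.45.
- 3,000 exposed: O/E becomes 1.49, 1.39 and 1.36.

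The pair with 400 exposed only just qualifies for grouping: its lower 90% IC limit is 0.001, and its lower 95% limit is −0.09, so alone it is not a signal.

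**The case against.** The strongest reply is that the article never says post-diagnosis prescriptions count. It is a condensed description, and index-date rules may sit in a fuller plan. That limits the point to what the stated rule does when applied as printed. But the exposure rule, the table, both thresholds and the grouping rule are all given, and together they produce the result above with no stated exception.

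The scope is narrow, and this part of the reply stands. The problem bites mainly on one of 15 outcome groups. Exposure ends with the pregnancy, so delivery, post-partum and infant outcomes largely follow it. The pre-pregnancy window is largely protected and the first trimester partly so. Treatments given only in hospital do not enter.

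The screen is also meant to be crude. Annotation, clinician review and adjusted cohort studies of three signals follow, and they would probably stop an obvious treatment from being selected. They come after groups and group means are formed, however, and nothing feeds them back.

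On grouping, a drug joins only if it already has a potential signal with every outcome in the group, so unrelated drugs are not drawn in.

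A reader might infer that women with depression, anxiety or psychosis before pregnancy are knowingly counted as cases. The article does not support that. The group is titled as conditions arising in pregnancy, and comorbidity at pregnancy start is extracted under Covariates, which points to incident disease. What is absent is a stated exclusion.

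**Conclusion.** The point holds for maternal medical conditions arising in pregnancy, in the trimester of diagnosis and later. There, treatments issued in primary care can outrank true threefold risks even when few cases receive them. This rests on assumed outcome and prescribing rates, but the direction is stable across the range tried. The damage is mainly to signal lists, rankings, attributable risks and group means. The grouping effect is material mainly for rarer drugs and depends on the unstated within-group variance. Those are the drugs that the Strengths section expects information sharing to help.

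A reader might go further and conclude that the strongest signals overall will be treatments, or that the three drugs finally studied will be wrong. The documents do not support either. Most outcome groups are little affected, and the expert review stands between the signal list and the final choice. The rule should be corrected before Objective 2 is run, but it does not undermine the project as a whole.

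**What to change.** For these dated maternal outcomes, state a time order and apply it before the IC and the bi-clustering.

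1. For each window, include only pregnancies free of the outcome when the window opens. For depression/anxiety/psychosis, also exclude women with a record of it at pregnancy start.
2. Count only outcomes first recorded after the window ends. Pregnancies with the outcome inside the window leave that table and are not treated as non-cases. This keeps the two-by-two Dirichlet model unchanged.
3. Where exposure and outcome share a window, count only prescriptions before the first outcome record, and give non-cases a matched gestational index date. The third trimester needs this, because its window closes with the pregnancy. Truncating cases alone would bias the IC downward. For example, if a rarely used drug with no effect is prescribed evenly over the window and cases on average lose half of it, then at a 5% outcome O/E = 0.5 / (0.05 × 0.5 + 0.95) = 0.51 and IC = −0.96.
4. Run the IC and the grouping on these counts only.

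Under the assumptions above, removing post-diagnosis prescriptions returns the drug with no effect to IC 0.01 (−0.25 to 0.24), while a drug with relative risk 2 keeps 0.99 (0.87 to 1.10).

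The cost is extra programming, most of it for the matched index dates, and some loss of same-window cases. Some leakage remains where a diagnosis code is entered after treatment has begun.
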